### Criteria for discontinuing or modifying allocated interventions {11b}

Discontinuing or modifying allocated interventions is not possible.

### Strategies to improve adherence to interventions {11c}

The sponsor-investigator is responsible to have written SOPs and WIs in place for the study and to provide those to all participating study sites. The principal investigators at all sites must have a manual of the relevant SOPs and WIs for the study on site and are responsible for proper training of all involved study personnel for the respective procedures*.* Adherence to intervention protocols will be controlled by recording the MORE sessions. EG, the founder of MORE, or KL will listen to the sessions to control for therapists’ adherence. To assess compliance with the intervention, we ask participants to report the mean time practice resp. meditation time per day, each week when they come for the MORE course. We will record the number of MORE courses completed for each participant and allow up to missing 2 MORE courses.

### Relevant concomitant care permitted or prohibited during the trial {11d}

FM participants will be withdrawn from the study if they receive treatment with medication affecting the central DA system, including opioids, neuroleptics, antileptics, antidepressive, and lithium, or if they have to undergo an examination with radiopharmaceutical or radioactive marked substances or if they begin another regular psychotherapeutic treatment or participate in another clinical trial during the course of the study until completion of the post-test measures. All other treatments are allowed during the course of the study. For healthy participants participating in PET measures at pre-test, the same conditions are applicable until the end of pre-test measures. For healthy participants not participating in the PET measures, the same conditions are applicable with exception of the examination with radiopharmaceutical or radioactive marked substance. Concomitant treatment will be recorded at each study visit in the eCRF.

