**Pain-related outcomes**					
Brief Pain Inventory (BPI, [15])		x	x	x	
Verbal Rating Scale for current Pain Intensity from SF-36 [70]		x	x	x	
Pain Disability Index [20]		x	x	x	

Before T1, we will perform the screening of the participants with regard to the inclusion and exclusion criteria (T0). Pre-test and post-test measures include each a 18F-DOPA PET scan at rest and a fMRI measure with the use of the reward task, the ambulatory assessment (AA) measures, the clinical and pain measures, and the fMRI measures. The follow-up consists in questionnaire assessments only, including the self-reported pain and clinical measures associated with PET and fMRI measures. The questionnaires will be presented through an online survey that is suitable for RCTs (Research Electronic Data Capture, RedCAP) and available at the Universities Fribourg and that can be filled at home.

The non-intervention FM control will undergo the same measures at pre-test and post-test, with a post-test planned on average after 8 weeks. They will not participate in any specific intervention, but will be given the opportunity to participate in MORE after the follow-up assessment (Fig. 1).

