### Intervention description {11a}

FM participants will participate in the MORE intervention or in a non-intervention control group. The non-intervention control group does not include any intervention. The MORE treatment is manual-based [28], consists of 8 sessions, and offers instruction in applying mindfulness and related skills to the following topics: discriminating between nociception, pain, and suffering; gaining awareness of automaticity and coping habits in chronic pain; disrupting the link between negative emotions, catastrophizing, and pain experience through reappraisal; refocusing attention from pain and life stressors to savor pleasant experiences; promoting acceptance instead of suppression of experience; and developing a mindful recovery plan. Mindfulness training will involve mindful breathing and body scan techniques, with an emphasis on developing metacognitive awareness and shifting attention from affective to sensory processing of pain and craving sensations. Sessions will be audio recorded for control of therapists’ adherence with the manual. MORE participants will be asked to engage in daily 15-min mindfulness practice sessions at home guided by a MP3 recording of the meditations. MORE is a manualized intervention that is centered on three therapeutic processes: mindfulness, reappraisal, and savoring. The MORE manual and the meditations are translated in French and in German. The non-intervention control group includes continuation of treatment as usual.

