#### Main primary outcome

1) A.18F-DOPA influx: the difference between FM patients and healthy controls at pre-test and between pre-test and post-test in FM

1) B. Measures of pain symptoms: the difference between FM patients and healthy controls at pre-test and between pre-test and post-test in FM in the scores of the 1-item Verbal Rating Scale (VRS) [70] and of the Brief Pain Inventory (BPI) [15].

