### Methods in analysis to handle protocol non-adherence and any statistical methods to handle missing data {20c}

Using an intent-to-treat analysis strategy allows to include all participants having completed the pre-test measures in case of drop-outs. In case of drop-outs, last observations will be carried forward.

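### Women withdrawn under the concomitant-care rule before post-test give no T2 or T3 questionnaires, so pain and clinical outcomes are lost for reasons plausibly tied to worsening, and neither planned analysis recovers them

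*Protocol article*

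**What the plan says.** Section 11d (relevant concomitant care) sets the rule: "FM participants will be withdrawn from the study if they receive treatment with medication affecting the central DA system". It names opioids, neuroleptics, antidepressives and lithium among these drugs, and adds an examination with a radioactive substance. It also applies "if they begin another regular psychotherapeutic treatment or participate in another clinical trial during the course of the study until completion of the post-test measures". The same section permits treatments outside this list and has concomitant treatment recorded at each visit.

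The comparator is usual care: "The non-intervention control group includes continuation of treatment as usual" (section 11a). Controls "will be given the opportunity to participate in MORE after the follow-up assessment" (text after Table 1).

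The Outcomes section lists pain under the main primary outcome: "1) B. Measures of pain symptoms: the difference between FM patients and healthy controls at pre-test and between pre-test and post-test in FM", scored by VRS and BPI. (The abstract places clinical pain measures among the secondary outcomes.) Questionnaires are completed online and can be filled in at home. At T3, "The follow-up consists in questionnaire assessments only".

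On women who leave, section 18b keeps the data collected before withdrawal, and section 22 asks those who stop early about adverse events. Section 20c states: "Using an intent-to-treat analysis strategy allows to include all participants having completed the pre-test measures in case of drop-outs", with last observations carried forward. The Discussion adds that drop-outs are replaced, and that complete datasets are analysed first and then compared with the intent-to-treat results.

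**The concern.** The rule operates after randomisation and removes a woman from the study because of something that happens during it. Entry requires three months free of drugs acting on the dopamine system, so a later antidepressant or opioid is a new start or a restart. Together with new psychotherapy, these are steps that a woman with worsening pain or mood would tend to take. The resulting loss of outcomes is then related to the outcomes themselves.

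Part of the rule clearly protects the 18F-DOPA measure. The online pain and clinical questionnaires remain measurable after any of the listed events, and no scan takes place at T3. The rule also ends at post-test. A woman who starts the same treatment the day after T2 still gives T3 data, while one who starts it the day before T2 gives neither T2 nor T3.

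At stake is the comparison of MORE with usual care on pain, mood and function at T2 and T3. Treatments that can begin in the course of usual care take women out of the arm that is meant to represent usual care, and this sits badly with the intent-to-treat aim.

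**Working it through.** **The plan's own figures.** The sample size section needs 20 per fibromyalgia group and allows 20% drop-out: 20/(1 − 0.20) = 25, which reproduces the stated 25. The final 32 per group tolerates a loss of 1 − 20/32 = 37.5% before falling below 20. This protects the number of completers. It does nothing about which women are missing. No figure in the document measures the withdrawal rule, so the rest is an illustration.

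**Assumptions (not in the documents).**
- Change from T1 to T2 is normal with SD 1, and higher means worse.
- Mean change is 0 in controls and −0.50 in MORE, so the true difference is 0.50 SD of change. The value echoes the d = 0.5 for pain severity in the sample size section, whose SD basis is not stated.
- Withdrawn fractions are p_M (MORE) and p_C (control). The correlation between worsening and withdrawal is ρ.

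**Formulas.** Let z be the 1 − p quantile of the standard normal and φ its density.
- Removing fraction p shifts the mean of the remaining women by ρ·φ(z)/(1 − p) in the favourable direction.
- Complete cases: difference = 0.50 − ρ·[φ(z_C)/(1 − p_C) − φ(z_M)/(1 − p_M)].
- Carried forward (a withdrawn woman has change 0): difference = 0.50·(1 − p_M) − ρ·[φ(z_C) − φ(z_M)].

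| p | φ(z) | φ(z)/(1 − p) |
|---|---|---|
| 0.05 | 0.103 | 0.109 |
| 0.10 | 0.176 | 0.195 |
| 0.15 | 0.233 | 0.274 |
| 0.20 | 0.280 | 0.350 |

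**Example, 5%/10%, ρ = 1.** Complete cases: 0.50 − (0.195 − 0.109) = 0.414. Carried forward: 0.475 − (0.176 − 0.103) = 0.402 (0.403 unrounded).

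| MORE/control withdrawn | ρ | Complete cases | Carried forward |
|---|---|---|---|
| 5%/10% | 0.5 | 0.457 | 0.439 |
| 5%/10% | 1 | 0.414 | 0.403 |
| 5%/15% | 0.5 | 0.417 | 0.410 |
| 5%/15% | 1 | 0.334 | 0.345 |
| 10%/20% | 0.5 | 0.423 | 0.398 |
| 10%/20% | 1 | 0.345 | 0.346 |
| 10%/10% | 0.5 or 1 | 0.50 | 0.45 |
| 20%/20% | 0.5 or 1 | 0.50 | 0.40 |

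A simulation under the same assumptions agrees to within 0.005.

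**Reading the table.** With more withdrawal in controls, both analyses shrink the difference. With equal rates, complete cases are about unbiased for the difference, while carrying forward still attenuates it, because withdrawn MORE women are scored as having gained nothing. If MORE women withdrew more often, the complete-case bias would reverse: 10%/5% with ρ = 1 gives 0.50 + (0.195 − 0.109) = 0.586.

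**The case against.** Several objections stand.

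- **Which arm loses more is unknown.** A reader might infer that untreated controls will be withdrawn more often. The document gives no rate by arm or by reason. The PET section lets MORE women be scanned from 6 weeks before the course starts until 14 weeks after, so up to 20 weeks may separate their T1 and T2, against about 8 for controls. Against that, randomisation precedes pre-test and controls are pre-tested while the MORE course runs, so they may wait longer before T1. Time at risk can differ in either direction.
- **The exposure is not 20 weeks for controls.** That is roughly the time from their pre-test to follow-up; the rule ends at post-test.
- **The bias could be read as much larger.** Removing the worst 10% to 20% of controls and no MORE women shifts the control mean by 0.10 SD (10%, ρ = 0.5) to 0.35 SD (20%, ρ = 1), that is 20% to 70% of 0.50. Only the net difference between arms biases the comparison, and 20% is the plan's whole drop-out allowance.
- **Not every escalation of care triggers withdrawal.** Other treatments are allowed, women with a psychiatric condition are excluded at entry, and the Discussion expects opioids to be of limited concern. Events may be few.
- **Not all of the rule concerns PET.** New psychotherapy or another trial can itself alter pain and mood. Whether the effect should include such treatment is partly a choice of estimand.
- **Women with pre-test data are not dropped from the intent-to-treat set.** True, and the two planned analyses are compared. But carrying forward replaces the missing value with no change, and the other analysis omits the woman, so agreement between them gives no reassurance: at 10%/20% with ρ = 1 both give about 0.35.

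These points limit the size and certainty of the problem. They do not supply the missing T2 and T3 values.

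**Conclusion.** The point holds as a gap in outcome collection. Withdrawal is from the whole study, nothing provides for later questionnaires, and neither carrying forward, analysing complete datasets nor replacing drop-outs restores what the randomised women would have reported.

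Under the assumed unequal rates, a true 0.50 SD of change is estimated at about 0.33 to 0.46 (complete cases) or 0.35 to 0.44 (carried forward). At equal rates the complete-case bias is about nil, and carrying forward gives 0.45 (10%) or 0.40 (20%). The likely bias is towards no difference, so the main risk is hiding a benefit. For complete cases, that direction depends on controls withdrawing more often, which the documents do not establish. The figures rest on assumed rates, normal change, no mean change in controls and a stated correlation.

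This is a cheap improvement to make while data are still being collected, since no later analysis plan can recover outcomes that were never asked for.

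**What to change.** Leave the list of triggering treatments, and the clinical and scanning rules, to the sponsor. State in sections 11d and 18b that a woman who meets a withdrawal criterion is, with her consent, still asked to complete the T2 and T3 online questionnaires, and that the event and its date are recorded.

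In the statistical methods, analyse VRS, BPI and the clinical scales as randomised including these data, and report the number and type of events by arm. An analysis excluding data after the event can be shown alongside.

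Section 11b says that discontinuing the allocated intervention is not possible, while 11d withdraws women from the study; the sponsor should reconcile the two.

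The cost is wording in a few sections and a few online questionnaires per affected woman. The downside is that the clinical estimate then includes the effect of other treatments started. That fits a treatment-as-usual comparator, and the accompanying analysis shows how much it matters.

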### Provisions for post-trial care {30}

Not foreseen.

### Outcomes {12}

To minimize bias, we will use only standardized questionnaires to assess the primary outcomes as recommended by Outcome Measures in Rheumatology Clinical Trials (OMERACT) [10].

#### Main primary outcome

1) A.18F-DOPA influx: the difference between FM patients and healthy controls at pre-test and between pre-test and post-test in FM

1) B. Measures of pain symptoms: the difference between FM patients and healthy controls at pre-test and between pre-test and post-test in FM in the scores of the 1-item Verbal Rating Scale (VRS) [70] and of the Brief Pain Inventory (BPI) [15].

#### Main secondary outcomes

2)The percent BOLD signal change in striatal activity during the reward task: the difference between FM patients and healthy controls at pre-test and between pre-test and post-test in FM patients3)The correlation between daily practice of mindful breathing and savoring (minutes) and increased striatal activity and 18F-DOPA influx4)Changes in pain-related and other clinical outcomes: the difference between FM patients-healthy controls at pre-test and between pre-test and post-test in FM on scores of quality of life (WHOQOL Brief [62];) and mood disturbances (State-Trait Anxiety Inventory (STAI [48];), Beck Depression Inventory (BDI)-II [43], Fibromyalgia Impact Questionnaire (FIQ [7];), Pittsburgh Sleep Quality Index (PSQI; [14]), and Emotion Regulation Questionnaire (CERQ; [51])5)Effects of the MORE intervention on self-reported pain, positive affect, and stress in daily life measured with AA: the difference between FM patients and healthy controls at pre-test and between pre-test and post-test in FM patients

### Participant timeline {13}

The overall study duration is 4 years from June 2021 to June 2025. Recruitment will take place during the entire study duration as we will perform 4 successive groups of the MORE intervention. The study duration per participant will be between 6 and 8 months, depending on scanner availability for the pre- and post-test measures. As soon as we have a minimum of 10 FM participants (minimum 5 participants and maximum 10 participants per MORE group), we will start with the first MORE group. The first measures will ideally be performed on healthy participants. The FM participants will be randomized after screening, and the ones assigned to the MORE intervention will undergo the pre-test measures of FM first. We plan 4 to 5 weeks to perform the pre-test measures for the participants allocated to the MORE group (2 participants per week). The first MORE will take place in the center where we will have first recruited the necessary number of participants. During the duration of the first MORE group (8 weeks), we will make the pre-test measures for the non-intervention control group and begin the pre-test measures for the second MORE group. This will allow us to begin with the second group as quickly as possible after the completion of the first group. During the second MORE group, we will perform the post-test measures for the first MORE group participants and test the non-intervention controls of the second MORE group. During fall 2021, we will test participants of the healthy control group and recruit the participants for the next two MORE groups that will take place in winter/spring 2022, according to a similar schedule for the first 2 groups. In parallel, we will perform the follow-up measures for MORE 1 and MORE 2. FM participants allocated to the non-intervention group will have the possibility to participate in a MORE group at the earliest after all participants of the group have completed follow-up measures, i.e., around 20 weeks after pre-test-measures (8 weeks delay for post-test measures + 12 weeks after post-test measures). In the years 2023 and 2024, we will complete the measures for the control group as well as the follow-up measures for the FM groups.

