## Assignment of interventions: allocation

### Sequence generation {16a}

We will use a simple randomization procedure with a blocked size of 5, 6, or 8 according to the recruitment flow. Randomization will be performed with an online program (sealed envelope, https://www.sealedenvelope.com) with the following randomization scheme: FMS MORE/FMS non-treatment control. The randomization will be performed for each group independently, before the pre-test measures by the data manager. Randomization tables will be deposited on RedCAP. There is no randomization of the healthy control groups for allocation in the PET or AA group.

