## Assignment of interventions: blinding

### Who will be blinded {17a}

Because there is no active control group or no placebo intervention in this study, the study staff and the participants will be unblinded.

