#### Ambulatory assessment measures and physiological measures

To investigate the effects of the MORE intervention on daily affects, stress, and reward experiences, we will use ambulatory assessment (AA) measures. Primary outcomes related to the AA measures include (1) self-reported measures of pain; (2) self-reported measures and physiological measures (CAR, alpha-amylase awakening, and daily profile of cortisol and alpha-amylase) of stress, (3) measure of positive affect, and (4) measures of reward experience. They will be compared between FM participants and healthy controls before the MORE intervention and before and after the MORE intervention between both FM groups. AA self-reports of pain, stress, and reward and positive experiences in daily life will be performed using an adaption of the Experience Sampling method [71] to assess the stress and reward experience in the daily living environment. The items related to pain are defined according to a pain diary that we have developed, tested, and validated in 50 chronic pain patients at the University of Fribourg. The self-reported items measuring stress, positive and negative affects, and reward experiences have additionally been adapted and validated in the framework of another research project [41]. All self-assessments are rated on a 7-point Likert scale. The participants will receive an iPod and perform self-assessments during 5 weeks five times a day, during the week preceding or following the PET measures before and after the MORE intervention. At the end of each day, participants randomly assigned to MORE will record the number of minutes spent engaged in the mindfulness, reappraisal, and savoring practices taught in the MORE intervention to provide a measure of adherence with the home practice associated with the MORE training. Biological measures of stress in everyday life will be assessed by collecting saliva samples 6 times a day (2 for cortisol awakening response (CAR) and for the salivary alpha-amylase (AA) awakening, 4 for daily profile) for a total of 3 days. Saliva samples will be obtained by using the passive drooling method (Salicap, IBL International Hamburg, Germany). Saliva samples will be stored overnight in the participant’s refrigerator. The saliva samples will be then sent to the Department of Psychology at the University Fribourg, where they will be stored at −20 °C in a freezer dedicated to research with restricted access. The CAR resp. AA awakening profile and the daily profiles will be used as biological indexes of stress reactivity in everyday life [71]. The outcome is the difference between pre-test and post-test and the comparison between the MORE group and the waitlist group. All samples will be sent for analyses at the end of the study.

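### Allocation is made, open-label, before any pre-test measure, so the self-reported baseline and the intent-to-treat set can depend on the arm, with size and direction unknown

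*Protocol article*

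**What the plan says.** **Order of events.** Participant timeline {13}: "The FM participants will be randomized after screening, and the ones assigned to the MORE intervention will undergo the pre-test measures of FM first". Sequence generation {16a} agrees: "The randomization will be performed for each group independently, before the pre-test measures by the data manager". Table 2 places allocation at t0 and the pre-test measures at t1.

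**Blinding.** Who will be blinded {17a}: "the study staff and the participants will be unblinded".

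**Timing by arm.** The MORE women are pre-tested over 4 to 5 weeks, two per week, before their course. For the controls, the timeline says: "During the duration of the first MORE group (8 weeks), we will make the pre-test measures for the non-intervention control group". The section on PET data acquisition, by contrast, gives a single pre-test window, from 6 weeks to 1 day before MORE begins.

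**Use of the baseline.** VRS and BPI are listed under Main primary outcome (item 1B, beside 18F-DOPA influx as 1A). Table 1 has them at T1, T2 and T3 only. They are analysed by a treatment group × time ANOVA.

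**Analysis set.** Section {20c} says that the intent-to-treat strategy "allows to include all participants having completed the pre-test measures in case of drop-outs", with the last observation carried forward. The Discussion instead describes intent-to-treat as covering everyone, to be compared with a complete-data analysis, and adds that drop-outs are replaced.

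**Ambulatory assessment.** Self-ratings are taken "during the week preceding or following the PET measures before and after the MORE intervention"; the same sentence also gives a duration of five weeks.

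**The concern.** A baseline is protected by randomisation when it is fixed before anyone knows the arm. Here a woman may rate her pain, mood and daily life at pre-test already knowing whether she will start MORE or wait, and the arm decides when she is tested. The Discussion itself accepts that knowing the assigned intervention can influence self-reported pain. It raises this for outcomes, but the schedule exposes the baseline too, and the baseline is one of the two time points in the main test.

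The analysis set has a related weakness. If intent-to-treat starts at completed pre-test, women lost between allocation and pre-test leave the comparison after randomisation. That step comes later for controls, so the loss could differ by arm.

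**Working it through.** **1. Is there a pre-allocation value for VRS and BPI?** No. Table 2 mentions self-report scales at screening, but Table 1 first schedules VRS and BPI at T1, after allocation at t0. The PET baseline is also at t1. No section states when a woman learns her arm. Early knowledge is inferred from the absence of blinding and from scheduling that follows the allocation.

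**2. How would a baseline shift enter the test?** Let b_pre and b_post be the between-arm differences in reporting caused by knowing the arm. The group × time contrast is (post − pre) in MORE minus (post − pre) in controls, so

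bias = b_post − b_pre.

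If the shift persists unchanged, it cancels. If it has gone by post-test, it enters in full. Either sign is possible.

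**3. Illustration of size.** The documents give no SD, no pre-post correlation and no shift, so all three are assumed. With no treatment effect and a net shift of s SD, the SD of change is √(2(1 − r)). The noncentrality of the two-sample t-test on change is [s/√(2(1 − r))] × √(n/2). For n = 32 and r = 0.5 this is (s/1) × 4 = 4s. Two-sided error at nominal 5%:

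| Net shift s | n = 32, r = 0.5 | n = 32, r = 0.7 | n = 20, r = 0.5 |
|---|---|---|---|
| 0.1 SD | 6.8% | 8.0% | 6.1% |
| 0.2 SD | 12.4% | 17.4% | 9.5% |
| 0.3 SD | 21.9% | 33.2% | 15.2% |

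The net shift is what counts. A 0.2 SD shift at pre-test of which 0.1 SD remains at post-test leaves 0.2 − 0.1 = 0.1 SD, so 6.8% rather than 12.4% in the first column.

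**4. Timing.** MORE pre-tests start 4 to 5 weeks before the course, and control pre-tests can fall as late as the end of its 8 weeks. The largest gap between two women of one cohort is 4 + 8 = 12 to 5 + 8 = 13 weeks. With the 6-week window of the PET section it is 6 + 8 = 14. A control tested while the course runs cannot meet a window that closes 1 day before it begins, so the two sections conflict.

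**5. Analysis set.** The plan's own inflation reproduces: 20/(1 − 0.20) = 25 per group, then rounded up to 32. The 20% comes from a trial's loss between start and completion of the intervention, so it does not describe loss between allocation and pre-test. A woman without a pre-test value has nothing to carry forward. Under the one stated method, the narrower wording of {20c} is therefore the set that could be analysed, and the Discussion's wording could not be carried out.

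If an arm lost a fraction q before pre-test, its mean baseline severity would fall by ρ·φ(z)/(1 − q) SD, where z is the (1 − q) normal quantile and ρ the correlation of severity with dropping out (all assumed). For q = 5%, 10% and 20% this gives 0.109, 0.195 and 0.350 SD at ρ = 1 (worst case), and 0.033, 0.058 and 0.105 SD at ρ = 0.3. A stable difference of this kind cancels in change scores. It biases group × time only if the women lost would also have changed differently.

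**6. Ambulatory week.** Read as one week, a PET on day −1 followed by 7 days of ratings ends on day −1 + 7 = 6 of MORE. At two scans per week, this could affect about the last two women scanned in each MORE group. The five-week figure in the same sentence leaves the true duration unclear.

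**The case against.** The strongest reply is that the order of events establishes a possibility and not a bias.

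- A reader might infer that any baseline shift passes whole into the treatment effect. It does not. Controls still know at post-test that they are waiting, and a persisting shift cancels. The direction is open too: controls who rate themselves worse at baseline and then recover would bias against MORE.
- A reader might cite the protocol's remarks on resentful demoralisation as evidence of a shift in waiting women. Those remarks concern placebo group interventions and argue against an active control. They say nothing about waiting-list baselines.
- A reader might assume that controls are lost more often before pre-test. No loss rate is given, and the offer of MORE after follow-up is a reason to stay.
- A reader might extend reporting bias to the first-listed primary outcome. 18F-DOPA influx is not self-reported.
- Section {20c} states whom the strategy allows to be included and contains no explicit exclusion rule, and the Discussion says everyone is included.
- The ambulatory overlap is an edge case in a secondary outcome, in a sentence that is itself unclear.

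All of these stand as limits on the claim. None of them supplies a pre-allocation value for VRS or BPI, aligns the pre-test timing of the arms, or reconciles the two descriptions of intent-to-treat.

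**Conclusion.** The point holds as a design weakness of unknown size and direction. Allocation comes before every pre-test measure in an open-label trial, so the self-reported baselines, including VRS and BPI, can be affected by knowing the arm. The group × time test is biased to the extent that this effect differs between pre-test and post-test. This rests on the inference that women learn their arm before pre-test. The error rates above are illustrations under assumed shifts and correlations, and do not estimate what will happen in this trial.

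Three further points are textual. Pre-test timing differs by arm by up to about 12 to 13 weeks and conflicts with the PET section's window. Section {20c} and the Discussion describe different intent-to-treat sets. On the one-week reading, a few pre-test ambulatory weeks could run into MORE. For 18F-DOPA the concern is confined to the timing difference and the selected analysis set. The changes are worth making because they are cheap. The documents do not support a claim that the results will be biased by a particular amount.

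**What to change.** 1. Have all women of a cohort complete the T1 questionnaires, at least VRS and BPI, online at home before allocation is generated and disclosed, and use these as the self-report baseline. Time the post-test questionnaires equally in both arms from that baseline.
2. Keep the PET/fMRI slots as planned. Optionally repeat the questionnaires at the PET visit, for the correlations with 18F-DOPA.
3. Reconcile {20c} with the Discussion so that intent-to-treat means all randomised women. The pre-allocation questionnaires make this workable for VRS and BPI. Report losses between allocation and PET by arm.
4. Keep the pre-test ambulatory week near the PET, but require it to end before session 1. Moving it ahead of allocation would separate it from the controls' PET by weeks and weaken the planned correlations. Reconcile the five-week and one-week durations in that sentence.
5. Reconcile the pre-test windows in the Participant timeline and the PET section.

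**Cost.** Allocation is disclosed slightly later in each cohort, and the online questionnaires may be repeated once. No visits or scans are added. If the baseline is taken before the first scan slot and the post-test at the end of the course, the self-report interval is about 12 to 13 weeks in both arms (4 to 5 plus 8), longer than the 8 weeks now planned for controls.
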